### Data analysis

Quantitative methods will be used to analyse patient, health services utilization and economic outcomes. Main and secondary outcome analysis will be based on all randomised wards and selected participants (intention-to-treat analysis). To account for within-patient correlation, due to multiple measurements from the same patient during assessment days, we will implement generalized estimating equation (GEE) models with binary outcome and logit link for all rate outcome comparisons [23]. The Cochran-Mantel-Haenszel (CMH) test will be used to compare proportions. Clustering effects for wards will be evaluated by calculating intraclass correlation coefficients and, if necessary, a fixed effect nominal factor will be included in GEEs to account for ward impact. A series of exploratory analyses will be conducted on subgroups and the impact of covariates on estimates of the effect of the intervention. A nonparametric median test will be used for HLOS comparison. In supportive analysis, HLOS will be considered as time to event data. Survival rates will be calculated and illustrated by the Kaplan–Meier method and further analysed by the log-rank test for univariate analysis (stratified by wards). Variables that reveal prognostic or effect modifying potential on the outcome as suggested by univariate analysis will subsequently be evaluated by the proportional Cox regression for multivariate analysis. Hazard ratios with the corresponding 95% confidence intervals will be reported. A *p* value of <0.05 is considered statistically significant. Data will be analysed using Stata version 14 or later [24].

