### Sample size

From a medical record review in one of the sites, the rate of adherence to escalation policy after abnormal VS measurement was 53% [6]. Sample size calculations are based on a 50% rate of adherence to escalation as per hospital policy. To detect a 20% improvement in adherence rate in the intervention group immediately following and 6 months post-intervention, 270 documented abnormal VSs per time point per study arm are required. Our sample size has been inflated to allow for a design effect of 1.5, accounting for within-patient autocorrelation and within ward clustering effect. Type I error is set at a 1% significance level accounting for multiple comparisons and study power is set to 90%. For secondary outcomes, we have 80% power to detect an odds ratio of at least 1.8 in post-intervention comparisons for an improved adherence rate in the intervention compared to the control group. For all other secondary outcomes, power calculations have been based on combining immediately following intervention and 6 months post-intervention data. For the unplanned ICU admission rate, a minimum of 0.3% difference (1.2 vs 0.9%); for MET call rate a minimum of 2.3% absolute difference (3 vs 0.7%); and at least 1.6 day (IQR = 20) median absolute difference (12 vs 10.4) for hospital LOS is detectable at 80% power. Due to a low incidence of cardio-respiratory arrests and hospital mortality, a power analysis is based on combining mortality and code blue, resulting in 80% power to detect a minimum 2.3% absolute difference (3 vs 0.7%).

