### Randomisation

Random 1:1 block randomisation of wards within hospitals to intervention or control groups will be undertaken. A central randomisation service independent of the study will be used with concealment until the intervention is assigned. Assessment days will be randomly selected.

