### Assessments

#### Aims 1 and 2

Outcome data collection will occur across three time points: at baseline prior to implementation, immediately following completion of the intervention (6 months) and 6 months post-intervention (12 months). At each time point, the medical records of all inpatients admitted to study wards will be reviewed by a RA (blinded to group allocation) to determine if abnormal VS were present, and if so, the rates of escalation as per hospital policy, HLOS, unplanned ICU admissions and unexpected inpatient mortality. Data collection days will be randomly selected. RAs will be trained in data entry. Prior to RAs collecting data independently, inter-rater reliability will be evaluated by the project manager who is a registered nurse with specialist intensive care qualifications. Independent data extraction will be conducted until >95% agreement is obtained. The secure data entry system will not allow invalid values; data backup measures will be installed. Costs attributed to FLIP and training will be calculated.

#### Aim 3

Facilitators will complete electronic activity logs; ward communication and policy changes will be collected by RAs electronically. To capture the experience of FLIPs and key stakeholders regarding the intervention and CPG implementation, semi-structured individual and focus group interviews and field observations will be conducted at critical points in the project—before, during and after the intervention. Interviews will be audio-recorded and transcribed verbatim.

All assessments are outlined in Table 1.

**Table 1 Tab1:** Data collection

Aim	Variable/Measure	Instrument	Outcomes	Data collection point
1	Adherence to CPG	eCRF	CPG element compliance: completed VS documentation; repeated VS within 30 min; interventions within scope of practice; CRC and MET activations; escalation as per hospital policy.	Baseline^a^, 6 and 12 months^b^
2	Patient outcomes	eCRF; Hospital clinical databases	Unplanned ICU admissions, cardio-respiratory arrests, limitations of medical treatment orders, HLOS and inpatient mortality.	Baseline^a^, 6 and 12 months^b^
2	Hospital costs	CRF; Hospital clinical costing databases.	Unplanned ICU admissions, HLOS and inpatient mortality; total cost of hospital episode.	Hospital episode^b^
2	Intervention costs	CRF; Staffing salaries	FLIP cost; training frequency	Continuous
3	FLIP dose	eACL	Contact and content of contact.	Continuous

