#### Cost analysis

Analysis of the costs of hospitalisation will be determined at the patient level over the 6-month period for intervention and control wards. All patients admitted to the study wards during the 6-month study period will be included in the analysis of mean total cost, HLOS and ICU LOS for intervention and control wards in each hospital. Only complete admissions will be included (patients admitted to a study ward and discharged from the hospital within the study period); and patients will be analysed based on their admission ward. Mean costs and HLOS for each patient in each ward will be compared to costs and HLOS for patients admitted to the same wards in the 6 months prior to the study period. Difference in difference analyses will be undertaken to compare the mean cost and HLOS difference between pre-intervention and intervention periods, and between intervention and control wards across hospitals. Costs will be attributed to the FLIP intervention based on the additional costs of the implementation process (staff time) over standard in-hospital CPG training.

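### The primary adherence model states no term for baseline ward adherence or for hospital, so the plan forgoes precision its own data could give; the loss is modest at the planned clustering.

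*Protocol article*

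**What the plan says.** Under Data analysis, the article commits to a model family for every rate outcome, the primary one included: "we will implement generalized estimating equation (GEE) models with binary outcome and logit link for all rate outcome comparisons". The reason given is repeated measurements on the same patient. The section adds a Cochran-Mantel-Haenszel (CMH) test for proportions without naming its stratum. It adds a fixed nominal factor for ward, to be used only if intraclass correlations suggest a need. The effect of covariates is placed among the exploratory analyses.

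Three other sections bear on this:

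- The Randomisation section sets the stratum: "Random 1:1 block randomisation of wards within hospitals to intervention or control groups will be undertaken".
- The Assessments section, for the first two aims, sets the rounds: "Outcome data collection will occur across three time points: at baseline prior to implementation, immediately following completion of the intervention (6 months"), with a further round at 12 months. Table 1 lists escalation as per hospital policy among the measures taken at baseline.
- The Cost analysis section uses the earlier period: "Difference in difference analyses will be undertaken to compare the mean cost and HLOS difference between pre-intervention and intervention periods". The same contrast is made by arm. Pre-intervention data on the same wards are thus given an explicit role for cost and length of stay, but none is stated for adherence.

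**The concern.** There are few randomised units. With about 18 wards per arm, the arms can differ by chance in how well their wards escalated care before the intervention began. A comparison of post-intervention rates alone carries that difference into the estimate. The trial collects the data that would correct for it, yet the stated model gives them no role. Likewise, an analysis that omits the stratum used in randomisation has a standard error that does not reflect the design.

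The ward fixed factor does not fill the gap as worded. Every ward belongs to one arm throughout, so with post-intervention rounds only, ward effects and the arm effect cannot be separated. At stake are power and the credibility of the estimate if the baseline audit shows the arms to be unequal.

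**Working it through.** **Inputs from the article**
- Sample size: a control adherence of 50%; a 20% improvement to be detected at each post-intervention round; a requirement stated as "270 documented abnormal VSs per time point per study arm are required"; a design effect of 1.5, covering correlation within patients and within wards together; type I error 1%; power 90%.
- Intervention group: 36 ward facilitators at two per ward, so 18 intervention wards and about 36 wards at 1:1. Setting gives 8 to 10 wards in each of four hospitals, so 32 to 40.

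**Assumptions.** The article gives neither the ICC nor the cluster autocorrelation (CAC, the correlation of a ward's true rate between rounds). Both are varied below.

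**1. The plan's own figure.** Take 50% versus 70%, two-sided 1%, 90% power, no continuity correction:

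n = [2.576·√(2·0.6·0.4) + 1.282·√(0.25 + 0.21)]² / 0.20² ≈ 176.1, so 177 per arm.

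Then 177 × 1.5 = 265.5, or 266, against 270 stated. The figure reproduces, and the 20% is therefore an absolute difference (50% versus 60% would need 1103). With 270/1.5 = 180 effective observations per arm, power is 90.7%.

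**2. Largest ICC the design effect allows.** Vital signs per ward m = 270/18 = 15. If all of the 1.5 is ward clustering, 1 + 14·ICC = 1.5, so ICC = 0.5/14 = 0.036 (0.031 at 32 wards, 0.040 at 40). Any within-patient correlation lowers this ceiling.

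**3. Chance imbalance in true ward adherence.** SE = √(0.25·ICC)·√(2/18).

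| ICC | Between-ward SD | SE of arm difference | 95% range |
|---|---|---|---|
| 0.036 (ceiling) | 9.4 points | 3.1 | ±6.2 |
| 0.05 (assumed) | 11.2 | 3.7 | ±7.3 |
| 0.10 (assumed) | 15.8 | 5.3 | ±10.3 |

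At the ceiling, the chance of an imbalance above 5 points is 11%, and above 10 points 0.15%.

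**4. Gain from baseline adjustment.** The variance is multiplied by 1 − r², where r = CAC·m·ICC / (1 + (m−1)·ICC). At ICC 0.036 and CAC 1.0, r = 0.54/1.504 = 0.359 and r² = 12.9%; at CAC 0.5, r² = 3.2%.

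| ICC | Variance reduction, CAC 0.5 to 1.0 | Power unadjusted | Power adjusted |
|---|---|---|---|
| 0.036 | 3.2 to 12.9% | 90.7% | 91.7 to 94.5% |
| 0.05 | 4.9 to 19.5% | 86.1% | 88.1 to 93.4% |
| 0.10 | 9.8 to 39.1% | 69.0% | 74.6 to 91.6% |

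**5. Hospital.** A ward-level simulation used four hospitals of nine wards, ICC 0.05 and a nominal 5% test. Ignoring hospital gave a type I error of about 5%, 4% and 3% when hospitals held 0%, 30% and 60% of the ward variance. Adjusting for hospital gave about 5% each time. The SD of the effect estimate was nearly the same either way.

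**6. The ward fixed factor.** With the two post-intervention rounds only, 36 ward columns, one for arm and one for time make 38 columns of rank 37: arm is a sum of ward columns. With the baseline round added, 36 ward, two time and two arm-by-time columns make 40, of full rank.

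**The case against.** The article condenses a fuller plan, and Data analysis gives a model family and link without listing its terms or saying which rounds enter. Silence is not exclusion, and adjustment terms are often left to an analysis plan. The CMH test is stratified by construction and may use hospital. A ward factor fitted with the baseline round would absorb both hospital and the ward's starting level. Planning difference in differences for cost does not oblige the same for adherence.

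Much of this stands. A reader might infer that the primary analysis definitely ignores baseline and hospital; the text supports only that it does not state their use. It still goes beyond silence: it places covariates in exploratory work and offers a ward term that fails unless the baseline round is included, which it never says.

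Other tempting readings also go too far:

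- **That the trial is exposed to large imbalance.** Under the plan's own design effect the 95% range is at most about ±6 points. Larger figures need an ICC above what that design effect allows.
- **That the estimate is biased.** Chance imbalance between randomised wards is sampling error, which a ward-clustered standard error covers.
- **That omitting hospital creates imbalance.** Blocking within hospital already balances it.
- **That each hospital has a different escalation policy.** The article refers to hospital policy but does not say that the four differ.
- **That baseline adjustment would remove 13%, 19% or 39% of the variance.** These are the upper ends and assume that ward differences persist perfectly between rounds.

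**Conclusion.** The point holds as an inexpensive improvement to the stated primary model, not as an error that threatens validity. At the ICC ceiling implied by the design effect, the expected gain is one to four percentage points of power, together with an estimate less open to challenge if baseline adherence differs between arms. If clustering is stronger than planned, the gain is material: at ICC 0.10, power of 69% would recover to between 75% and 92%. Those figures rest on 36 wards, 15 vital signs per ward, and the assumed ICC and CAC. For hospital, the consequence of omission is a conservative test, and only if hospitals differ in adherence. The ward fixed factor needs correction whatever the ICC, because as worded it is usable only with the baseline round in the model.

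**What to change.** Specify the primary GEE with arm, hospital (four levels) and the ward's baseline adherence, for example as an empirical logit. Alternatively, include the baseline round with arm-by-time terms and no arm difference at baseline. In that form the working correlation must link a ward's rounds, because under working independence the baseline round would not adjust the later comparison. Base inference on clustering by ward, replacing the conditional ward fixed factor. State the stratum of the CMH test. The same model form can serve the other practice rates.

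This needs no new data. Three hospital contrasts and one baseline covariate use four of roughly 34 ward-level degrees of freedom (36 − 2), leaving about 30.

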#### Secondary outcomes

The secondary outcomes are as follows: *Nursing practice*: Nurses’ adherence to CPGs measured by proportions of documented VS (complete set), repeated VS within 30 min of obtaining an abnormal VS and documented nursing scope of practice interventions in response to abnormal vital signs; proportions of activated urgent clinical reviews and MET calls in patients fulfilling the criteria. *Clinical:* Rates of cardio-respiratory arrests, unplanned admissions to ICU, unexpected hospital mortality and mean HLOS. *Costs:* Mean additional cost of implementing the intervention and mean/median total hospital cost and HLOS for patients. *Process evaluation*: measurement of the fidelity of the facilitation intervention, contextual influences and impact on ward processes and practice.

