### Setting

Four hospitals in Victoria, Australia, will be the setting for this study. All are acute, major metropolitan teaching hospitals that have more than 400 beds, employ over 1300 nurses and cover both acute and specialist services. Sponsorship for the study was sought from the Executive Directors of Nursing and Chief Executive Officers of each hospital prior to the funding application. Within each hospital, eight to ten wards will be randomly allocated to either intervention or control groups; the intervention will be delivered at ward level. Each ward is considered a cluster for the purpose of analysis. Wards will be eligible for inclusion if they contain 18 or more beds and they receive support from the hospital’s MET. Critical care, emergency, paediatrics, maternity, peri-operative and psychiatric areas will be excluded because they use an alternative response system for patient deterioration.

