### Intervention group

The intervention group ward staff will receive the standard implementation of CPGs as described above plus the facilitation intervention for practice improvement (FLIP). FLIP comprises individuals in facilitator roles using facilitation methods and processes in a flexible way to tailor implementation strategies to the local ward context, according to identified barriers and enablers.

There will be two types of internal facilitator roles: hospital facilitators (HFLIP) and ward facilitators (WFLIP). A hospital facilitator will be appointed to cover four or five intervention wards in each of the four hospitals, acting as the overall facilitation lead and coordinator and mentor for the ward facilitators in each hospital. In each intervention ward, two ward facilitators will be appointed to support and enable ward nurses to implement the CPGs into practice (*N* = 36). Each HFLIP will be prepared and supported by an external expert in facilitation (GH). Each HFLIP will work with eight to ten WFLIPs. The facilitation intervention is underpinned by the PARIHS [14, 16] and i-PARIHS [21] frameworks.

Training and a toolkit of methods and techniques will be given to all FLIPs to promote the transfer of CPGs into daily practice. The intervention wards will receive 5 h per week support from the HFLIP for 6 months, reviewing barriers and enablers to implementing CPGs into practice prior to intervention commencement and in discussion with the WFLIPs. The HFLIP will provide face to face interactive education, including small group work, case presentations and role play, as well as review ward specific systems, processes, routines and audit practices in order to align systems of care to enable implementation of CPGs into daily practice. At ward level, the two WFLIPs will work with the HFLIP to audit practice, identify barriers, strategies and goals for improvement. They will provide cover for each other during leave and support ward staff during practice hours, receiving one day per fortnight of protected time for conducting audits, facilitation of ward nurses and meeting with the HFLIP to agree on strategies to improve adherence to guidelines.

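### The Data analysis section names an unadjusted Cochran-Mantel-Haenszel test for proportions in a ward-randomised trial, which inflates type I error for the nursing-practice outcomes

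*Protocol article*

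**What the plan says.** All references are to the protocol article.

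- **Randomisation:** "Random 1:1 block randomisation of wards within hospitals to intervention or control groups will be undertaken".
- **Setting:** "Each ward is considered a cluster for the purpose of analysis".
- **Sample size:** "Our sample size has been inflated to allow for a design effect of 1.5, accounting for within-patient autocorrelation and within ward clustering effect".
- **Data analysis, first method:** "we will implement generalized estimating equation (GEE) models with binary outcome and logit link for all rate outcome comparisons". The reason given there is repeated measurements on the same patient.
- **Data analysis, second method, in the next sentence:** "The Cochran-Mantel-Haenszel (CMH) test will be used to compare proportions". No strata, role or cluster adjustment is given.
- **Data analysis, ward effect:** intraclass correlations will be calculated and, if judged necessary, a fixed ward factor will be added. That step is confined to the GEEs.
- **Secondary outcomes:** adherence elements (complete vital sign sets, repeat vital signs within 30 min, nursing interventions) are measured as proportions, as are "proportions of activated urgent clinical reviews and MET calls in patients fulfilling the criteria".

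**The concern.** The article acknowledges clustering when it sets the sample size and when it motivates the GEE, then names for proportions a test whose standard form assumes independent observations. The outcomes it calls proportions are the nursing-practice outcomes, which are recorded on patients nursed together in randomised wards and partly on repeated vital signs from the same patient.

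If the test is run as named, its variance is too small and its p values are too low. A chance difference between wards would be reported as an effect of the facilitation intervention more often than the stated significance level allows.

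**Working it through.** **Inputs**
- Adherence without the intervention 50%; improvement 20%, read as 20 percentage points (50% v 70%); type I error 1%; power 90%; 270 abnormal vital signs per arm per time point; design effect (DE) 1.5. All from Sample size. Sidedness is not stated; two-sided is assumed.
- Significance threshold: 1% in Sample size, 5% in Data analysis. Both are shown below.
- Number of wards: two ward facilitators per intervention ward and 36 facilitators in all (Intervention group), so 36 / 2 = 18 intervention wards. With 1:1 allocation, 18 per arm is assumed.

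**Step 1. Is 1.5 really the planning figure?**

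n = [z(0.995)·√(2·0.6·0.4) + z(0.90)·√(0.5·0.5 + 0.7·0.3)]² / 0.2²

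= [2.576·0.693 + 1.282·0.678]² / 0.04, which rounds up to 177 per arm.

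177 × 1.5 = 266, within 2% of the stated 270. The figure is reproduced, so the DE of 1.5 is a working input to the trial's size.

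**Step 2. Size of a test that ignores the design effect**

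If the true variance is DE times the variance the test assumes, the real two-sided error is 2·[1 − Φ(z(1−α/2)/√DE)].

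At DE = 1.5, √DE = 1.225:
- nominal 5%: 1.960 / 1.225 = 1.600, real error 10.95% (2.2 times nominal)
- nominal 1%: 2.576 / 1.225 = 2.103, real error 3.55% (about 3.5 times nominal)

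Across other values of DE:

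| DE | Real error at nominal 5% | Real error at nominal 1% |
|---|---|---|
| 1.0 | 5.0% | 1.0% |
| 1.2 | 7.4% | 1.9% |
| 1.3 | 8.6% | 2.4% |
| 1.5 | 10.95% | 3.55% |
| 2.0 | 16.6% | 6.9% |

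The error doubles only when DE reaches (1.960/1.645)² = 1.42 at nominal 5%, or (2.576/2.326)² = 1.23 at nominal 1%.

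**Step 3. Does stratification rescue the CMH test?**

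*By hospital.* Simulation under no effect: 18 wards per arm in four hospitals (4, 4, 5 and 5 per arm), 270 / 18 = 15 observations per ward, beta-binomial outcomes with mean 0.5, ICC = (1.5 − 1)/(15 − 1) = 0.036, and 40,000 runs. The hospital-stratified CMH test rejected in 10.9% of runs at nominal 5% and 3.7% at nominal 1%. With DE = 1 the same code gave 5.2% and 1.0%, so the excess comes from the clustering.

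*By ward.* Not possible. Each ward lies wholly in one arm, so in a ward stratum the observed count equals its expectation and the variance term is zero. Such strata carry no information on the arm comparison.

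**Step 4. Which outcomes are exposed?**

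| Outcome | Called a proportion | Called a rate |
|---|---|---|
| MET calls | Secondary outcomes | Sample size |
| Adherence to the guidelines | Secondary outcomes (nursing-practice elements) | Sample size |
| Escalation per policy (primary) | nowhere | Sample size, Assessments |

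The nursing-practice outcomes fall under the CMH sentence by the article's own label. The primary outcome does not, but the first two rows show that the labels do not separate outcomes reliably. Table 1 also lists escalation with the other adherence elements under a single compliance heading.

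**The case against.** A reader might infer that the primary outcome is given two competing tests and so two p values, of which either could be reported. The text does not support that. Escalation is always called a rate, and the GEE is assigned to all rate comparisons. Reaching CMH requires the reader's own step that a rate of adherence is computed as a proportion. The loose vocabulary permits that step, but the article does not prescribe it. Nor can it be said that the nursing-practice outcomes are tested by CMH alone, since adherence and MET calls are also called rates. Which test takes precedence is something a condensed article may leave to an analysis plan that is not shown, so its absence here is not a fault.

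A reader might also infer that the error rate is at least doubled. That is not a bound: at nominal 5% it fails for any DE below 1.42. The 1.5 is a planning allowance for abnormal vital sign records, combining repeated measures and ward clustering. It need not carry over to patient-level proportions such as MET calls in eligible patients, which lack the repeated-measures component.

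These points limit the scope and size of the problem but do not remove it. A later plan can add detail to an incomplete method, but here the article positively names a test. Its standard form is anti-conservative at every DE above 1, and the only ward adjustment mentioned does not reach it.

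**Conclusion.** The point stands for the secondary nursing-practice outcomes. The article names a test without cluster adjustment for outcomes it calls proportions, in a trial that randomises wards and was sized on the premise that observations are correlated.

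If the DE is the planned 1.5, the real error is about 11% at nominal 5% and 3.55% at nominal 1%; between a DE of 1.2 and 2.0 it runs from 7.4% to 16.6% at nominal 5%. These figures assume two-sided tests and a CMH test in standard form. The simulation further assumes equal ward sizes and places all the correlation at ward level.

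For the primary outcome the conclusion is weaker: on a literal reading it goes to the GEE, and the wording merely fails to exclude CMH clearly. This should be fixed, but it does not by itself undermine the primary analysis.

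**What to change.** In Data analysis:

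- Remove the unadjusted CMH test as an inferential test for comparisons between arms.
- State that the decision p value for escalation adherence, and for every nursing-practice proportion, comes from a model that accounts for ward clustering.
- Report raw proportions by arm and time point descriptively.
- If a CMH-type test is still wanted, use a cluster-adjusted form and label it supportive.
- Use one term, rate or proportion, for each outcome throughout, so that the assignment of methods cannot be misread.

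The text change is small and needs no new data. Because the article makes ward adjustment in the GEE conditional, that wording must be brought into line with the second item. The statistical cost is p values less favourable than an unadjusted CMH would give; they would be consistent with the design effect already built into the sample size.

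### Wards are randomised, but the GEE is set up for within-patient correlation, and ward enters only conditionally, as a fixed effect aliased with arm

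*Protocol article*

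**What the plan says.** Three sections of the protocol article treat the ward as the unit that matters.

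- Randomisation: "Random 1:1 block randomisation of wards within hospitals to intervention or control groups will be undertaken".
- Setting: "Each ward is considered a cluster for the purpose of analysis".
- Sample size: the design effect of 1.5 is said to cover both autocorrelation within patients and clustering within wards.

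The Data analysis section departs from this. It gives the purpose of the GEE as "To account for within-patient correlation, due to multiple measurements from the same patient during assessment days". For wards, ICCs are calculated first, and then "if necessary, a fixed effect nominal factor will be included in GEEs to account for ward impact". No threshold for necessity is given. The same section adds: "The Cochran-Mantel-Haenszel (CMH) test will be used to compare proportions".

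For adherence, the Sample size section powers a comparison of the arms at each of the two post-intervention time points. A difference-in-difference contrast is stated only under Cost analysis, for cost and length of stay.

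**The concern.** When wards are randomised, the error of the arm comparison includes variation between wards, whatever a sample ICC happens to show. An ICC estimated from a few dozen wards is imprecise, so a small estimate is weak evidence that ward can be ignored. Making the adjustment depend on it also makes the choice of primary model data-dependent.

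The remedy named for the other case does not do the job either. A nominal ward factor takes up all differences between wards, and the difference between the arms is one of these. So one outcome of the rule risks a p value that is too small, and the other removes the comparison that the trial was powered for. What is at stake is the validity of the primary result.

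**Working it through.** **1. The plan's own figure.** "Sample size calculations are based on a 50% rate of adherence to escalation as per hospital policy". The 20% improvement is read as 50% v 70%, with alpha 1% two-sided and power 90%.

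n = [2.576·√(2·0.6·0.4) + 1.282·√(0.5·0.5 + 0.7·0.3)]² / 0.2² = (1.785 + 0.869)² / 0.04 ≈ 176.1, so 177 per arm.

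177 × 1.5 ≈ 266, close to the stated 270. The planned number therefore already includes the claimed allowance for wards.

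**2. Number of wards.** Setting: "Within each hospital, eight to ten wards will be randomly allocated to either intervention or control groups". Four hospitals give 32 to 40 wards. Intervention group: "two ward facilitators will be appointed to support and enable ward nurses to implement the CPGs into practice", 36 facilitators in all. So there are 36/2 = 18 intervention wards, about 36 wards in total at 1:1, and 270/18 = 15 abnormal vital signs per ward per time point.

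**3. If ward is left out.** Let DE be the factor by which the true variance exceeds the variance that a patient-clustered GEE estimates. The actual type I error is 2·[1 − Φ(z/√DE)]. The article does not split its 1.5, so DE is shown as a range. Both significance levels appear because Sample size uses 1% and Data analysis uses 0.05.

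| Residual ward DE | Actual error at nominal 5% | Actual error at nominal 1% |
|---|---|---|
| 1.0 | 5.0% | 1.0% |
| 1.1 | 6.2% | 1.4% |
| 1.25 | 8.0% | 2.1% |
| 1.5 | 11.0% | 3.5% |

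The last row attributes the whole 1.5 to wards, which implies an ICC of (1.5 − 1)/(15 − 1) = 0.036 (0.031 to 0.040 for 16 to 20 wards per arm). As a middle case, assume two records per patient with correlation 0.25. The patient part is then 1.25, the remainder is 1.5/1.25 = 1.2, and the error is about 7.4% (1.9% at nominal 1%).

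A null simulation gives the same direction (36 wards, 8 patients with 2 records each, assumed latent patient ICC 0.2, 1,500 runs):

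| Assumed latent ward ICC | Patient-clustered, 5% / 1% | Ward-clustered, t on 34 df, 5% / 1% |
|---|---|---|
| 0 | 5.4% / 0.7% | 5.1% / 0.7% |
| 0.02 | 7.7% / 2.3% | 6.3% / 1.1% |
| 0.05 | 9.5% / 3.0% | 4.1% / 0.8% |

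The Monte Carlo standard error near 5% is √(0.05·0.95/1500) ≈ 0.6 percentage points.

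**4. If ward is a fixed effect.** Each ward lies in one arm, so the dummies of the intervention wards add up to the arm indicator. With 36 ward dummies (and time indicators where there is more than one time point), adding a column leaves or changes the rank of the design matrix as follows.

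| Data used | Column added | Rank before | Rank after |
|---|---|---|---|
| One time point | arm | 36 | 36 |
| Both post-intervention points | arm | 37 | 37 |
| All three points | arm | 38 | 38 |
| All three points | two arm-by-time terms | 38 | 40 |

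The arm main effect is not estimable in any of these. If software drops ward columns instead of arm, the coefficient labelled arm is a contrast between reference wards. A change-from-baseline contrast is estimable.

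**5. Would that contrast rescue the rule?** It was simulated with ward fixed effects, patient-level clustering, baseline and one later time point (800 runs). The error at nominal 5% is 5.6%, 7.4% and 12.6% for an assumed ward-by-time ICC of 0, 0.02 and 0.05. It holds its level only if ward effects are stable over time.

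**The case against.** The strongest reply is that the article condenses a longer plan, and that several severe readings go beyond its text. Four of these need limits.

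- A reader might infer that the ward fixed effect leaves no treatment effect at all. The documents do not support that. The same wards are audited at baseline, 6 and 12 months, and an arm-by-time contrast survives ward fixed effects. What is lost is the between-arm main effect after the intervention. That is the comparison powered under Sample size, and no baseline-adjusted contrast is stated for adherence.
- A reader might take it as fixed that the GEE clusters on patient. The article names no cluster variable; this is inferred from the stated purpose of the GEE. If ward was intended, Data analysis must say so, because as written it conflicts with Setting.
- A reader might quote error rates above 11%. Those need ward clustering beyond what a total design effect of 1.5 allows. The calculation also assumes that ward is ignored throughout, whereas the rule ignores it only when the ICC looks small. The figures describe that branch and not the whole conditional procedure.
- A reader might infer that the CMH test gives a second, anti-conservative p value for the primary outcome. The article does not say that CMH is applied to individual vital-sign records, to the primary outcome, or with which strata.

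The core remains. The article itself names the model's purpose, the trigger and the remedy, so this is a stated rule and not detail left to another document.

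**Conclusion.** The Data analysis section contradicts the Setting, Sample size and Randomisation sections, and neither outcome of its ward rule is sound for the comparison that the trial is powered on.

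- With ward omitted and clustering on patient, the type I error is about 6% to 11% at nominal 5%, or 1.4% to 3.5% at nominal 1%. This rests on an assumed residual ward design effect of 1.1 to 1.5. At a ward ICC of 0 there is no inflation, but the plan's own design effect assumes that ward clustering exists.
- With ward as a fixed effect, the post-intervention arm effect is not identifiable. This follows from the design and needs no assumed ICC. The surviving arm-by-time contrast is unstated for adherence and would be anti-conservative under patient-level clustering if ward effects vary over time.

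This should be corrected before the analysis, because it decides whether the primary p value is valid.

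**What to change.** - Make ward the GEE cluster unconditionally. Patients are nested in wards, so this also covers repeated records on a patient.
- Use a small-sample-corrected sandwich variance and a t reference based on the number of wards. With about 36 wards that is 36 − 2 = 34 degrees of freedom, or 31 after three hospital terms. A mixed logistic model with ward and patient random effects is an acceptable alternative.
- Include hospital, since randomisation was blocked within it.
- Delete the ICC-dependent rule and the ward fixed effect, and report the ICC descriptively.
- Restrict any CMH test on clustered records to description.

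The cost is a change of wording and somewhat wider confidence intervals. The planned 270 per arm per time point is unchanged, because its design effect of 1.5 already claims ward clustering.
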